### Experimental protocol

#### Overview

Having read the participant information sheet (Additional file 1) and discussed the study in its entirety with a member of the research team (IT), potential participants will be guided through the process for providing written informed consent (Additional file 2). Following this, eligibility will be assessed by a series of self-report questionnaires together with a BMI calculation. Eligible participants will then undergo the 8-week protocol shown in Fig. 1a. All lab sessions will be completed at the University of Bath (Somerset, UK) whilst all other aspects of the study will occur under free-living conditions. In preparation for all laboratory sessions, participants will avoid caffeine, alcohol, smoking and strenuous exercise throughout the preceding 24 hours, whilst also standardising their dietary intake. Following an overnight fast (minimum 10 hours) participants will report to the laboratory at 07:30 ± 01:00 having consumed 500 mL of water upon waking. Female participants will schedule all laboratory sessions to coincide with the follicular phase of their menstrual cycle (i.e. 3–10 days after onset of menses) to account for monthly fluctuations in hormone levels and the associated changes. A SPIRIT figure showing the schedule of enrolment, assessment of outcome measures, allocation and interventions across the 8-week timeline is shown in Fig. 2, and the accompanying SPIRIT checklist can be found in Additional file 3.

**Fig. 1 Fig1:**
[figure not shown]
Schematic of the 8-week study design (**a**) and the sampling intervals for laboratory sessions 2 and 3 (**b**). *DEXA* dual-energy x*-*ray absorptiometry

**Fig. 2 Fig2:**
[figure not shown]
SPIRIT 2013 figure showing schedule of enrolment, assessments, allocation and intervention for each participant. *NEFA* non-esterified fatty acids, *PYY* peptide YY, *DEXA* dual-energy x-ray absorptiometry

#### LAB 1 (baseline)

This initial lab session will provide a reference point for examining the stability of body mass, as an indicator of overall energy balance, throughout the ensuing 4-week monitoring phase in which habitual dietary intake and physical activity are quantified. In addition, this visit will serve to familiarise participants with key procedures to improve reliability over subsequent laboratory sessions [41, 42]. Specifically, this will involve the provision of a urine sample to measure hydration status before both height and body mass are measured. Resting metabolic rate and substrate oxidation will be quantified using indirect calorimetry of expired air samples, after which a fasted blood sample shall be drawn from the antecubital vein to measure baseline concentrations of certain biomarkers (e.g. glucose, cholesterol). To conclude this session, a supervised submaximal treadmill protocol will also be undertaken to individually calibrate the physical activity monitors being used throughout the study (Actiheart™).

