#### Monitoring phase

During this 4-week phase, participants will be asked to maintain their habitual diet and activity patterns. Within this, both energy intake and physical activity will be measured concurrently in four designated monitoring windows of 3 consecutive days each. These windows will be separated by at least 2 days and the final window will coincide with the 3 days leading up to LAB 2. Data on physical activity energy expenditure and intensity will be captured using individually calibrated Actiheart^TM^ monitors [43, 44], whilst energy intake will be measured by means of a weighed record of food and fluid intake. To proceed into the next phase, participants will be required to maintain energy balance throughout the monitoring phase and provide accompanying measurements of energy intake and expenditure. Energy balance will be ascertained by maintaining a stable body weight (<1.0 kg increase or decrease) between LAB 1 and LAB 2 [16, 45].

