#### LAB 2 (pre-intervention)

Having completed the monitoring phase, participants will then return to the laboratory for measurement of a series of fasted and postprandial outcomes. Once again, hydration status will be ascertained from a urine sample before body mass is measured. As discussed previously, if body mass differs from the value recorded in LAB 1 by more than 1.0 kg then participants will be asked to repeat the monitoring phase. Providing this criterion is satisfied, then fasting measurements of resting metabolic rate and substrate oxidation will be repeated before a cannula is fitted to an antecubital vein and a fasting venous blood sample is drawn. In order to examine changes at the tissue level, a subcutaneous adipose tissue biopsy will also be obtained from the abdominal region at this time. The last of these fasted measurements will be a set a visual analogue scales and computer-based tasks to assess perceived hunger, fullness, desire to eat and food preferences. This will then be followed by two sequential test meals. The first will feature indirect calorimetry measurements from expired gases, visual analogue scales/computer tasks, and venous blood samples, whereas the second will only involve sampling of arterialised venous blood. Figure 1b shows the sampling intervals for the various measurements. Blood samples will be used to examine both postprandial nutrient handling (e.g. glucose, insulin, triglyceride concentrations) and appetite regulation (e.g. ghrelin, peptide YY concentrations). To conclude, a DEXA scan will be performed to measure pre-intervention fat and lean tissue mass.

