#### Intervention phase

During a 6-day rest following LAB 2, which is included to avoid prolonged periods of monitoring [46] and maintain the 4-week testing interval, participants will be randomised to one of the three parallel intervention arms outlined in Table 1. The three diet groups will last for 20 days each with transitions between 24-hour cycles occurring at 15:00 each day. Not only does this transition point allow the consumption of at least one main meal per day to aid motivation, but more importantly, it also ensures that the latter and more demanding part of the fast coincides with diurnal reductions in appetite to encourage adherence [47]. Furthermore, this structure still gives a full 24-hour fasting period, which is around double that achieved in most prior studies [8].

**Table 1 Tab1:** Intervention arms employed in the study protocol

Intervention	Description
Daily calorie restriction	Reduce normal intake by 25% every day
Intermittent fasting with calorie restriction	Alternate between 24-hour periods of fasting and feeding with 150% of normal intake on fed days
Intermittent fasting without calorie restriction	Alternate between 24-hour periods of fasting and feeding with 200% of normal intake on fed days

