### Indirect calorimetry

Resting metabolic rate and substrate oxidation in both the fasted and postprandial state will be measured using indirect calorimetry of expired air samples [49]. In each instance, three consecutive 5-minute air samples will be collected using a mouthpiece and the Douglas bag method (Hans Rudolph, MO, USA) before analysis (Servoflex MiniHF 5200, Servomex, UK) and evacuation (Dry Gas Meter, Harvard Apparatus, MA, USA). Samples will be collected in accordance with best practice guidelines [50], with the values from two or more samples that agree to within 100 kcal/day averaged and used in further analysis [37], along with the corresponding substrate oxidation parameters. During the treadmill test for the calibration of activity monitors, a single 1-minute air sample will be collected per stage for which a facemask shall be used in place of the mouthpiece for participant comfort.

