### Data analysis

As outlined in the aims of the present study, the primary outcomes will explore the effects of the intervention on postprandial glucose/insulin responses (pre–post) and energy balance – reflected by changes in resting metabolic rate (pre–post), physical activity energy expenditure (monitoring–intervention) and postprandial thermogenesis (pre–post). Secondary outcomes will explore changes from pre- to post-intervention in body composition, substrate oxidation, lipid profile, leptin concentration, c-reactive protein concentration, adipose tissue gene expression, postprandial lipaemia and postprandial appetite regulation/perception. In addition, differences in physical activity intensity and dietary composition between the monitoring and intervention phases will be examined. As it is not the objective of this study to compare these differences between the cohorts, two sets of analyses will be conducted on a per protocol basis -– one for the lean cohort and one for the overweight/obese cohort. Both will centre upon a two-way mixed model analysis of variance featuring a factor for diet allocation and a factor for time-point. This will permit an examination of the effect of each diet on the outcomes of interest (i.e. pre vs. post/monitoring vs. intervention) and whether this effect varied between the three dietary conditions. Pre-existing differences between groups at baseline will be examined using a one-way analysis of variance featuring a factor for diet allocation. Significant differences emerging from these tests will be explored using appropriate post-hoc tests to adjust for multiple comparisons and isolate the source(s) of variance. In addition to these analyses at the group level, individual responses will also be closely scrutinised to examine whether outliers could be affecting the interpretation. Further analysis, such as sub-group analysis, may also be conducted in light of patterns emerging in the final dataset. Baseline characteristics of participants who withdraw during the intervention will also be compared against the final population using *t* tests. Statistical significance will be accepted at *P* < 0.05.

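### Resting metabolic rate is measured twice before randomisation, but the between-diet comparison uses only the second value; adding the first as a covariate is a cheap efficiency gain of uncertain size

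*Protocol article*

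**What the plan says.** All places are in the Methods of the protocol article.

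- **LAB 1 (baseline):** "Resting metabolic rate and substrate oxidation will be quantified using indirect calorimetry of expired air samples". The section gives this visit two purposes: a reference for body mass, and familiarisation meant to make later sessions more reliable.
- **LAB 2 (pre-intervention):** "fasting measurements of resting metabolic rate and substrate oxidation will be repeated before a cannula is fitted".
- **Overview:** "In preparation for all laboratory sessions, participants will avoid caffeine, alcohol, smoking and strenuous exercise throughout the preceding 24 hours". The overnight fast, arrival window and follicular-phase scheduling likewise apply to every session.
- **Indirect calorimetry:** "In each instance, three consecutive 5-minute air samples will be collected using a mouthpiece and the Douglas bag method".
- **Monitoring phase:** energy balance between the two visits is judged by "maintaining a stable body weight (<1.0 kg increase or decrease) between LAB 1 and LAB 2".
- **Intervention phase:** in the rest period after LAB 2, "participants will be randomised to one of the three parallel intervention arms outlined in Table 1".
- **LAB 3 and Data analysis:** LAB 3 repeats the LAB 2 protocol to give the pre–post comparison. Energy balance is a primary outcome, "reflected by changes in resting metabolic rate (pre–post") among other components. The model is a two-way mixed ANOVA with factors for diet and time-point.

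No use of the LAB 1 RMR in that comparison is stated.

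**The concern.** With one pre and one post value, the diet-by-time interaction in a mixed ANOVA is the same test as a one-way ANOVA on the change LAB 3 minus LAB 2. All of the session-to-session noise in LAB 2 therefore enters each participant's change. A second fasted RMR, taken by the same method under the same stated preparation and before allocation, goes unused.

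The between-diet contrast serves the study's first aim (compensation under fasting compared with daily restriction) and its third. The Power calculation, however, sizes the trial at 10–12 per arm for within-treatment effects only. Precision for the between-diet contrast is therefore scarce, and here some may be available without another participant, visit or assay.

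**Working it through.** **1. The plan's own figure.** The Power calculation gives RMR 1898 (SD 262) before and 1670 (SD 203) after, a difference of 228 kcal/day, and n = 11 for 80% power at two-sided 0.05. It states no pre–post correlation. Assuming r = 0.5:

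SD of change = √(262² + 203² − 2 × 0.5 × 262 × 203) = √56,667 = 238; 228/238 = 0.958; a paired t test then needs 11.

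The figure reproduces at r = 0.5. At r = 0.3 the answer would be 14, and at r = 0.7 it would be 8. This shows what the sample size implies; it is not evidence about the repeatability of RMR.

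**2. Set-up.** Take equal variance (set to 1) at the three visits, and correlation r between LAB 1 and LAB 2 and between LAB 2 and LAB 3. Two patterns for LAB 1 with LAB 3:

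- equal correlation: r
- decay: r². This is natural because the visits are about equally spaced: 4 weeks of monitoring, then a 4-week testing interval.

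Residual variances for the diet contrast:

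- Planned change score: 2(1 − r)
- LAB 3 adjusted for LAB 2: 1 − r²
- LAB 3 adjusted for LAB 2 and LAB 1, equal correlation: 1 − 2r²/(1 + r)
- LAB 3 adjusted for LAB 2 and LAB 1, decay: 1 − r², because LAB 1 adds nothing once LAB 2 is known

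**3. Results.**

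| r | Gain from LAB 1 beyond LAB 2, equal correlation: (1+2r)/(1+r)² | Same, decay | Both covariates vs change score, equal correlation: (1+2r)/[2(1+r)] | Same, decay: (1+r)/2 |
|---|---|---|---|---|
| 0.5 | 0.89 | 1.00 | 0.67 | 0.75 |
| 0.7 | 0.83 | 1.00 | 0.71 | 0.85 |
| 0.8 | 0.80 | 1.00 | 0.72 | 0.90 |
| 0.9 | 0.78 | 1.00 | 0.74 | 0.95 |

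So LAB 1 itself removes 0% to 11–22% of residual variance. Moving from the planned analysis to both covariates removes 5–25% (decay) or 26–33% (equal correlation). In the decay column the whole gain comes from adjusting for LAB 2 instead of subtracting it.

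**4. Why covariates and not an average.** The variance of change from the mean of LAB 1 and LAB 2 is 1.5(1 − r) under equal correlation, 25% below 2(1 − r). Under decay it is 1.5 − 0.5r − r². At r = 0.5 this equals 1.00 against 1.00 (no gain). At r = 0.9 it is 0.24 against 0.20, which is 20% more variance. If only the error variance of LAB 1 is larger, by a factor k, averaging gives (1 + (1 + k)/4)/2 of the single-baseline variance, which reaches 1.00 at k = 3. A fitted coefficient gives LAB 1 less weight in these cases; a fixed average cannot.

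**5. Cost of the covariates.** Each takes one error degree of freedom. Estimating q slopes also inflates the expected variance of a pairwise difference by (ν − 1)/(ν − q − 1), where ν = N − 3 for three arms. With N = 30–36, ν = 27–33. Going from one covariate to two multiplies the variance by 25/24 to 31/30, about 3–4%. In the least favourable cell above (decay, r = 0.9), both covariates against the change score give 0.95 × 26/24 = 1.03 at N = 30 and 0.95 × 32/30 = 1.01 at N = 36. That is roughly break-even.

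**The case against.** **Nothing in the plan is wrong.** Taking the last value before randomisation as pre is standard and unbiased, and a full analysis plan could add covariates. This stands, and it is why the point is only an efficiency improvement. It can still be raised because the article fixes both the pre value and the model.

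**LAB 1 is not an interchangeable replicate.** It is a familiarisation visit at least about 4 weeks before LAB 2, longer if monitoring is repeated, so its values may be shifted, noisier or less correlated with LAB 3. This stands against averaging. It does not defeat the covariate form: both values precede allocation, so a first-visit shift is common to the arms in expectation, and the fitted coefficient reflects how informative LAB 1 proves to be.

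**A stronger reading is tempting.** A reader might infer that the two visits are exact replicates and that LAB 2 alone carries 33–43% more variance than necessary (33% with equal SDs, 43% with the planning SDs at r = 0.5, where averaging lowers the SD of change from 238 to 199). The documents do not support this. It needs equal correlation across all three visits, which the protocol nowhere gives, and an equally reliable LAB 1, which sits badly with that visit's stated purpose.

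**No gain in power can be quoted.** Such a figure would need a between-diet difference. The 228 kcal/day in the Power calculation is a whole within-arm effect, and the Discussion describes fasting with restriction and daily restriction as isocaloric, so nothing supports that size for their contrast.

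**Extension to other outcomes is weak.** Body mass is already constrained to within 1.0 kg between visits. Blood at LAB 2 and LAB 3 comes through a cannula, which is not described for LAB 1.

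**Conclusion.** The point holds as an inexpensive efficiency improvement for one primary outcome. Two fasted pre-randomisation RMR values are collected under the same stated method and preparation, and the planned between-diet comparison uses one.

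The size is uncertain. For r = 0.5–0.9 with equal SDs, LAB 1 adds between nothing and an 11–22% reduction in residual variance beyond LAB 2. Replacing the change-score analysis by adjustment for both gives 5–25% under decaying correlation and 26–33% under equal correlation. These are ranges under assumed correlations, before the small cost of estimating the slopes. If LAB 1 is much noisier than LAB 2, its own contribution will be small. The planned analysis is valid, and no bias in the diet contrast is claimed.

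**What to change.** In Data analysis, add a sentence fixed before the data are analysed: for the between-diet comparison, LAB 3 RMR is analysed with diet as a factor and LAB 2 and LAB 1 RMR as covariates, separately in each cohort. Keep LAB 2 alone as pre for the within-arm change, where a familiarisation shift at LAB 1 would matter. Do not average the two visits.

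The cost is one error degree of freedom per covariate and, for the second covariate, about 3–4% in expected variance if LAB 1 proves uninformative. The between-diet and within-arm results for RMR would then come from two stated analyses instead of one ANOVA, and the text should say so. No new data are needed.

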#### Monitoring phase

During this 4-week phase, participants will be asked to maintain their habitual diet and activity patterns. Within this, both energy intake and physical activity will be measured concurrently in four designated monitoring windows of 3 consecutive days each. These windows will be separated by at least 2 days and the final window will coincide with the 3 days leading up to LAB 2. Data on physical activity energy expenditure and intensity will be captured using individually calibrated Actiheart^TM^ monitors [43, 44], whilst energy intake will be measured by means of a weighed record of food and fluid intake. To proceed into the next phase, participants will be required to maintain energy balance throughout the monitoring phase and provide accompanying measurements of energy intake and expenditure. Energy balance will be ascertained by maintaining a stable body weight (<1.0 kg increase or decrease) between LAB 1 and LAB 2 [16, 45].

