For the IMF groups, during fasted cycles, participants are only permitted water, herbal teas and black tea/coffee with no sugar (i.e. unsweetened energy-free drinks). During feeding cycles, and throughout the daily calorie restriction diet, participants will appropriately modify their normal diet to give 75%, 150% or 200% of their habitual daily energy intake (measured during monitoring phase) in accordance with the group they are assigned to. Participants will also continue to monitor their physical activity and energy intake over the first and last 6 days of the intervention period. In the context of physical activity, this is to examine behavioural adaptations to the different diets; therefore, participants are allowed to adjust the quantity of activity/exercise undertaken based on how they feel, but are instructed not to incorporate any unfamiliar activities. In contrast, measurements of energy intake will be used to monitor compliance with intake targets with feedback provided to maximise accuracy. It is anticipated that, for some participants, doubling the volume of their habitual diet to achieve the calorie target whilst maintaining macronutrient balance will not be feasible. In these circumstances, achieving the required calorie intake will take precedence over maintaining macronutrient balance, both of which will be reported in resulting publications.

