#### LAB 3 (post-intervention)

Following the completion of 20 consecutive 24-hour dietary cycles, participants will be required to standardise their diet and activity levels for 1 day to match those reported in the lead up to previous lab sessions and eliminate any residual effects of the final diet period. As with LAB 1 and LAB 2, this will also involve avoiding caffeine, alcohol, smoking and strenuous exercise before completing an overnight fast (minimum 10 hours) and consuming 500 mL of water upon waking. At 07:30 ± 01:00, participants will return to the laboratory and repeat the protocol outlined earlier for LAB 2, thereby providing a pre–post comparison.

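### One of the 12 baseline activity days falls under the pre-LAB 2 exercise ban and the recorded intervention days have no equivalent, which can slightly mask a within-arm fall in activity

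*Protocol article*

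**What the plan says.** The Data analysis section of the protocol article lists PAEE, compared between the monitoring and intervention phases, among the primary outcomes.

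For the baseline, the Monitoring phase section sets "four designated monitoring windows of 3 consecutive days each" and fixes the last of them: "the final window will coincide with the 3 days leading up to LAB 2". During this phase "participants will be asked to maintain their habitual diet and activity patterns". The Overview adds a rule for all laboratory sessions: "participants will avoid caffeine, alcohol, smoking and strenuous exercise throughout the preceding 24 hours".

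For the intervention, activity is recorded "over the first and last 6 days of the intervention period", and in that time "participants are allowed to adjust the quantity of activity/exercise undertaken based on how they feel" (Intervention phase). The same section states the calendar: "The three diet groups will last for 20 days each with transitions between 24-hour cycles occurring at 15:00 each day". The matching preparation for the final visit comes afterwards: "Following the completion of 20 consecutive 24-hour dietary cycles, participants will be required to standardise their diet and activity levels for 1 day" (LAB 3).

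**The concern.** Two baseline instructions pull against each other on one day. Participants are to live as usual, and on the day before LAB 2 they are also to avoid strenuous exercise. That day is recorded. The corresponding day before LAB 3 lies outside the recorded intervention windows. A baseline mean over all recorded days is therefore held down by protocol in people who normally exercise hard, and the intervention mean is not.

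The first objective asks whether intermittent fasting provokes compensatory changes in energy balance, such as a fall in activity. A lowered baseline makes such a fall look smaller. The affected comparison, before versus during within a diet, is also the kind of effect on which the Power calculation section bases its 10–12 participants per arm. More participants would not remove an offset of this kind.

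**Working it through.** **Plan's own figures.** The plan gives no effect size, standard deviation or sample size for PAEE. Its sample sizes are 11 (resting metabolic rate) and 9 (two-hour glucose). A two-sided paired t test at 5% and 80% power reproduces both if the pre–post correlation is assumed to be 0.5 (standardised differences 0.958 and 1.097). This confirms that the sizing rests on within-arm change. It says nothing about the variability of PAEE, so the offset is not converted into lost power here.

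**Restricted days in each phase.**
- Baseline: 4 windows × 3 days = 12 days. The last window ends at LAB 2, so 1 of 12 days (24 of 288 hours, 8.3%) is under the ban.
- Intervention: 6 + 6 = 12 days, with no ban stated.
- Calendar check: 6 rest days + 20 diet days + 1 standardisation day = 27, so LAB 3 falls on day 28 after LAB 2. This agrees with the 4-week testing interval given in the Intervention phase section and puts the standardisation day outside the windows.
- The 15:00 transition: if the last cycle ended at 15:00 on the day before a 07:30 visit, the ban would overlap the last recorded window from 07:30 to 15:00. That is 7.5 of 288 hours (2.6%). The share of waking time would be larger, but it is still part of a day against a whole day at baseline, so the direction is unchanged.

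**Size of the offset.** Let s be the share of a participant's habitual PAEE that comes from strenuous exercise. If that exercise is skipped on the restricted day, the day yields on average (1 − s) of the habitual value, and the 12-day mean is too low by s/12. A true fall f then appears as 1 − (1 − f)/(1 − s/12). The values of s and f are assumptions:
- s = 5%: baseline low by 0.4%. A true 10% fall appears as 9.6%, a true 5% fall as 4.6%.
- s = 10%: baseline low by 0.8%. These appear as 9.2% and 4.2%.
- s = 20%: baseline low by 1.7%. These appear as 8.5% and 3.4%.
- s = 0: no offset.

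**If the session is moved instead.** Suppose it moves to one of the other two days of the final window. The 12-day total is then unchanged and the 12-day mean is right. Dropping only the restricted day leaves (12 − (1 − s))/11 = 1 + s/11 of the habitual value, too high by 0.5% at s = 5% and 1.8% at s = 20%. Dropping the whole final window (9 days left) avoids both errors.

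**Effect on PAL.** Assume 150–600 kcal/day of habitual strenuous exercise. The shift is 150/12 = 12.5 to 600/12 = 50 kcal/day. Divided by the 1898 kcal/day resting rate quoted in the Power calculation section, that is 0.007–0.026 PAL units, which matters only for someone that close to the 1.75 cut-off.

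**The case against.** The strongest reply is that the article never says baseline PAEE is the mean of all 12 days. Which recorded days enter the average is a derivation rule that an analysis plan, not shown here, may settle. This stands in part. The error is not certain, but the article itself fixes the window against the visit, describes the phase as habitual, and excludes nothing. Using the data as recorded produces the offset.

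Second, the size is small and wholly assumed. That stands. The ban covers strenuous exercise only, so walking, work and light activity continue. The Physical activity section lets participants omit the running stage so that the sample is not tilted towards formal exercisers, and many may therefore have little to lose.

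Third, sessions may be moved rather than skipped, in which case the obvious correction introduces a small error the other way. That also stands and shapes the remedy.

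A reader might infer that a primary outcome is biased throughout, in every arm and in the comparison of diets, or that stratification is compromised. The documents do not support this. All arms share the same monitoring schedule before randomisation, so the diet-by-time contrast is unbiased in expectation. Any change of PAL stratum also happens before allocation and does not bias randomised comparisons.

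**Conclusion.** The asymmetry is in the text: 1 of 12 baseline days is restricted, against at most a few hours of the 12 recorded intervention days. It lowers baseline PAEE by s/12 among participants who normally do strenuous exercise and skip it rather than move it to another monitored day. For an assumed s of 5–20% that is about 0.4–1.7%. The consequence is a slight masking of a within-arm fall; between-arm contrasts are not biased and the effect on PAL stratification is negligible. The result rests on averaging all recorded days and on an assumed s, since the documents contain no activity data. It would be too strong to conclude that the trial could miss real compensation for this reason: no PAEE variability is given against which to judge an offset of this size. This is a minor point, worth acting on because correction is cheap.

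**What to change.** Derive the primary baseline PAEE and physical activity intensity without the 24 hours before LAB 2. Keep recording that day, but use it only as the template for standardisation before LAB 3. Report two sensitivity analyses of the monitoring-to-intervention change: one with all 12 baseline days, and one omitting the whole final window, which guards against a session moved within it. The PAL used for stratification can stay as it is.

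The monitors give minute-by-minute estimates, so this needs no new data or visits and can be applied to participants already enrolled. The cost is 11 baseline days rather than 12 in the primary derivation and 9 in one sensitivity analysis. If days are treated as independent, the day-to-day part of the variance of a participant's baseline mean rises by a factor of 12/11 = 1.09 or 12/9 = 1.33. A small bias in the opposite direction (up to s/11) also remains possible in the 11-day mean where sessions were displaced.
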